### Adverse events

AEs are defined as adverse medical events that occur after the subjects or their guardians provide written informed consent until the end of the study visit. AEs include abnormal laboratory results, symptoms, or diseases. All AEs will be recorded on a Case Report Form (CRF) and the researcher should provide comprehensive clinical reports. Once AEs occur, we will follow the principle of “the first priority of the participants,” take the necessary treatment according to the patients’ specific situation, and decide whether to suspend the clinical research. The main investigator should immediately inform the Scientific Research Office, Medical Service, and Ethics Committee of CHCMU. The SAE report should be submitted in writing within 24 h, while a follow-up SAE report should be submitted to the Human Research Ethics Committee.

An insurance policy will be prepared for all participants, who will be provided with ancillary and post-trial care in the case of injury or death as a result of their participation in the trial.

### Outcome evaluation

The outcome measures and their time frames of this trial are listed in Table 3. The primary endpoint is the cumulative duration of oxygen therapy, i.e., the duration from starting to stopping oxygen treatment.

**Table 3 Tab3:** Outcome measures

Measures			Time frames
Primary outcomes	Cumulative duration of oxygen therapy		Until the time of stopping oxygen therapy
Secondary outcomes	Adverse events	Number of serious adverse events	Within 24 h post hUC-MSCs infusion
		Acute infusion associated adverse events	From the start of the trials to 1 month post hUC-MSCs infusion
		Late infusion associated adverse events	Within 2 years post hUC-MSCs infusion
	The rate of supplemental oxygen therapy		At 1 month post hUC-MSCs infusion
	Duration of invasive mechanical ventilation		
	Duration of noninvasive mechanical ventilation		
	The first time of stopping oxygen supplement		
	The rate of re-oxygen supplement		
	Pulmonary function changes		At 6, 12, and 24 months post hUC-MSCs infusion
	Chest radiography changes		
	Blood oxygen saturation		At 1, 3, 6, 12, and 24 months post hUC-MSCs infusion
	Mortality		
	Times of hospital readmissions		
	Complications of preterm birth		

The secondary endpoints include the safety and efficacy outcomes. The safety of the study will be assessed by the number of AEs including SAEs, acute infusion-associated AEs (AIA-AEs) and late infusion-associated AEs (LIA-AEs). SAEs include death, any malignant cardiac event (new ventricular tachycardia, ventricular fibrillation, or asystole, cardiac arrest), acute pulmonary embolism, stroke, anaphylactic shock, acute transplant rejection, and any other diseases extending the hospital stay. AIA-AEs include fever, general allergic reaction (rash, edema, erythema, pallor), infection at the injection site, vital sign changes, laboratory test changes (indicators of liver and kidney function, cardiac markers, indicators of hematology and immunity, markers of hepatitis/syphilis/HIV/tuberculosis, and urinalysis). LIA-AEs include tumorigenic events (tumor formation) and teratogenic events.

The efficacy endpoints are as follows: duration of oxygen therapy, duration of invasive mechanical ventilation, duration of noninvasive mechanical ventilation, the first time stopping the supplemental oxygen, rate of re-oxygen supplement, blood oxygen saturation, chest radiography changes, pulmonary function changes, mortality, number of hospital readmissions, and preterm birth complications.

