### Sample size and calculation

The sample size of this phase-II randomized controlled trial was calculated by power analysis using the Power and Sample Size online calculator (http://powerandsamplesize.com/). The trial is designed to investigate the hypotheses of two interventions compared to control, but it is not powered to test differences between the two intervention groups. The larger of the two numbers is the sample size of this trial. The primary outcome measure is the change in the cumulative duration of oxygen therapy. The cumulative mean duration of severe BPD is reportedly 90 ± 15 days [4, 31]. This trial is powered to identify differences of 15% (from 90 days in the control group to 77 days in the low-dose groups) and 20% (from 90 days in the control group to 72 days in the high-dose groups) in participants who accept the hUC-MSC intervention. Meanwhile, the power is set at 0.8, type I error *ɑ* is 0.05, and type-II error *β* is 0.20. The calculated sample size is 21 for each group. To account for the possibility of 10% of patients being lost to follow-up, the final sample size will be 24 and the total size will be 72.

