### Inclusion and exclusion criteria

The inclusion and exclusion criteria are listed in Table 1. Participants will be 0–1 year of age. The diagnostic criteria and BPD severity gradation refers to the criteria established by the NICHD workshop [5]. The Silverman and Andersen score is used to assess the severity of abnormal respiratory manifestations [32].

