### Recruitment

Patients can only be enrolled in this study after passing the citywide consultation resolution and signing the informed consent form.

Participants will be recruited from three sources. First, the parents of potentially eligible hospitalized patients diagnosed with severe BPD will be approached and asked to join this study. Second, physicians will generate lists of patients from the electronic medical records of CHCMU with a diagnosis of BPD who were discharged within 1 year. Investigators or physicians will contact the patients’ parents by telephone or mail them a research leaflet and recruitment letter. Third, physicians will post study flyers at the outpatient department, the official website, and the WeChat public platform of CHCMU for those diagnosed with severe BPD at other hospitals. If the parents of these patients with severe BPD are interested in this research, we will initiate the screening process.

A multidisciplinary consultation will be held to confirm whether these potential participants meet the general diagnostic criteria of BPD as well as the inclusion and exclusion criteria. The consultation will consist of a neonatologist, a respiratory physician, a radiologist, a laboratory physician, a Department of Critical Care Medicine expert, stem-cell treatment center researchers, and medical department staff. If more than 80% of experts agree on the hUC-MSCs treatment, these patients will be viewed as potential participants. The researcher will then arrange a meeting to communicate with the legal representative or parents about the clinical trial research details and sign the written informed consent form.

The following details of the clinical trial will be fully explained to the patients’ guardians as follows: (1) study purpose; (2) research background; (3) number of participants and duration of their participation; (4) study procedures; (5) potential discomfort and risks of treatment; (6) expected benefits; (7) protection of confidentiality and privacy; and (8) their participation is voluntary. Each patient’s legal representative or parents will sign the informed consent form after all the items above are fully understood. After that, the patients’ baseline characteristics will be recorded by the clinicians (Table 2).

**Table 2 Tab2:** Timeline and items of evaluation during the trial

Items		Study period									
		Screening phase	Treatment phase				Follow-up phase				

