### Randomization and blinding

Participants will be randomized into three groups in a 1:1:1 ratio after collection of the baseline data. The allocation sequence will be generated and sent to the investigators by a statistician. Participants will not be blinded during the phase-II trial and the patients in the control group will not be given hUC-MSC treatment.

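### The primary outcome counts oxygen days from before randomisation in infants enrolled up to age 1 year, and the planned mean, SD and power are not supported for that population

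*Protocol article*

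**What the plan says.** The section Outcome evaluation defines the outcome: "The primary endpoint is the cumulative duration of oxygen therapy, i.e., the duration from starting to stopping oxygen treatment". Table 3 gives its time frame only as "Until the time of stopping oxygen therapy", an end with no start. Several secondary outcomes in the same table are timed from the infusion.

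On entry, the section Inclusion and exclusion criteria states: "Participants will be 0–1 year of age". One recruitment source is patients "with a diagnosis of BPD who were discharged within 1 year". Table 1 asks for severe BPD, a Silverman-Anderson score above 3 and consent; being on oxygen or ventilatory support at entry is not a listed criterion. On timing: "Participants will be randomized into three groups in a 1:1:1 ratio after collection of the baseline data".

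On planning, the section Sample size and calculation states: "The cumulative mean duration of severe BPD is reportedly 90 ± 15 days". It plans for 77 days (low dose) and 72 days (high dose) against 90, with power 0.8 and α 0.05, giving 21 per group, 24 after 10% loss, and 72 in total. That section calls the primary outcome a change in cumulative duration, which is not how Outcome evaluation defines it.

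The section Statistical analysis compares duration of oxygen therapy between groups by t test and names no covariate. The secondary outcomes include the "rate of re-oxygen supplement".

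**The concern.** If the clock starts when oxygen starts, part of each infant's outcome has already accrued at randomisation and no allocation can alter it. The later an infant enters, the larger that part. Savings of 13 and 18 days must then come entirely from the days that remain, so a treatment that shortens the remaining time by a given percentage shows a smaller percentage on the total.

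The planning figures raise a second doubt. A mean of 90 with SD 15 describes a narrow distribution, and entry up to 1 year admits infants whose prior oxygen time alone could lie beyond it.

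A third doubt is internal. A cumulative duration and a single start-to-stop interval differ once oxygen is resumed, and the trial expects that to happen because it lists re-oxygenation as an outcome. At stake is whether 72 infants can answer the primary question.

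**Working it through.** **1. Reproduce the plan.** Inputs from Sample size and calculation: SD 15; differences 90 − 77 = 13 and 90 − 72 = 18 days; α 0.05, taken as two-sided; power 0.80.

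- n per group = 2 × (1.96 + 0.8416)² × SD² / difference²
- Low dose: 2 × 7.849 × 225 / 169 = 20.9, so 21
- High dose: 2 × 7.849 × 225 / 324 = 10.9, so 11
- The larger is 21; 21 / 0.9 = 23.3, so 24; 3 × 24 = 72

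The arithmetic is right.

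**2. Slack.** By the same normal approximation, power at 21 per arm is 0.802 for 13 days and 0.973 for 18 days. The largest SD that keeps 80% power is 15.04 days for the low dose and 20.8 days for the high dose. By t test, the planned method, power is 0.78 and 0.97.

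**3. Fit to the population.** If durations are roughly normal, 90 ± 2 × 15 puts about 95% of totals between 60 and 120 days. Entry is allowed up to about 365 days of age. An infant with more than 90 oxygen days at randomisation is already above the planned control mean and cannot finish at 77 or 72 days. The article does not say that 90 ± 15 comes from infants enrolled across the first year.

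**4. Sensitivity to the SD.** The article gives no age or prior-oxygen distribution at entry, so SDs above 15 are assumptions. They stand for enrolled infants who differ from the source of the 90 ± 15. Two-sided t test, α 0.05, 21 per arm:

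| SD of total (days) | Power, 13 days | Power, 18 days |
|---|---|---|
| 15 (plan) | 0.78 | 0.97 |
| 20 (assumed) | 0.54 | 0.81 |
| 25 (assumed) | 0.38 | 0.62 |
| 30 (assumed) | 0.28 | 0.48 |

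With all 24 per arm evaluable, the low-dose column becomes 0.84, 0.60, 0.42 and 0.31.

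**5. Dilution at the plan's own SD.** Assume that 45 of the 90 days have passed at randomisation.

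- If the planned proportional reductions (13/90 = 14.4% and 18/90 = 20%) act only on the remaining 45 days, the savings are 6.5 and 9 days. Power at SD 15 and 21 per arm is then 0.28 and 0.48.
- To save 13 and 18 days in full, the remaining time must fall by 13/45 = 29% and 18/45 = 40%. If 60 days have passed, the figures are 13/30 = 43% and 18/30 = 60%.

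**6. Would moving the clock alone help?** Simulate total duration as normal with mean 90 and SD 15, with randomisation at a uniform time over 0–30, 0–60, 0–90 or 0–365 days while still on oxygen. The SD of the total stays at 14.4 to 15.0. The SD of days counted from randomisation is about 17, 23, 27 and 28. Under the plan's own SD, unadjusted post-randomisation days are therefore noisier than the total. Total days equal prior days plus later days, so once prior days enter as a linear covariate, both outcomes give the same treatment estimate. The gain in precision comes from the adjustment.

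**The case against.** The strongest reply is that 90 ± 15 is stated for the cumulative duration itself, so it already includes whatever accrues before randomisation. Varying the day of randomisation does not widen the total. This stands: it would double-count to add a separate pre-randomisation variance to 15 and read off a power loss. The SD exceeds 15 only if the enrolled infants differ from those behind the cited figure, which the article neither shows nor rules out. A reader might infer that SD 15 and 80% power are impossible here. The documents do not support that, since with early enrolment the SD could be near 15.

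A reader might also infer that infants already weaned will be enrolled with their outcome fixed. That too goes beyond the text. A Silverman-Anderson score above 3 is required, eligibility is checked again at baseline, more than 80% of a multidisciplinary panel must agree to treatment, and discharged does not mean off oxygen. Weaned infants are less likely but not excluded, and one who resumed oxygen would still add days on a cumulative count.

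Third, Table 2 lists oxygen therapy only from baseline, so a start at baseline might be intended. The definition does not say so.

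Last, randomisation balances prior oxygen time in expectation, the trial calls itself exploratory, and covariates are often left to an analysis plan. The comparison is indeed unbiased. The start of the clock and the handling of re-starts, however, belong to the endpoint definition that the article itself states.

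**Conclusion.** The point holds in a limited form. Read as written, the primary outcome includes oxygen days before randomisation, and the stated t test makes no allowance for them. The consequence is dilution and uncertain precision; it is not bias. The sample size follows from its inputs, but those inputs are unsupported, and probably optimistic, for infants enrolled up to age 1 year.

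The size of the loss cannot be fixed from the article. It depends on age and oxygen history at entry, which are not given, so the powers at SD 20 to 30 and the case with 45 days remaining are illustrations. What does not depend on them is the lack of margin: the low-dose comparison sits at 0.80 by normal approximation or 0.78 by t test, and any SD above about 15 takes it lower. The high-dose comparison is more robust to the SD (0.81 at SD 20), though not to dilution (0.48 with 45 days remaining). The ambiguity over re-started oxygen stands regardless of these assumptions.

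**What to change.** - Define the primary outcome as all days on oxygen from randomisation to a fixed day, summing re-started episodes, and use that definition in Outcome evaluation, Table 3 and the sample-size section.
- Adjust the primary comparison for oxygen days before randomisation and for age at randomisation. This part is essential, because moving the clock alone may raise the variance.
- Reconcile Table 1 with the endpoint: state whether infants must be receiving oxygen or ventilatory support at randomisation, and make the outcome definition agree with the answer.
- Restate the SD, effect and power for the redefined outcome, label them as assumptions, and show a range.

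The article reports that recruitment had not begun at submission, so the change is cheapest before the first infant is randomised. It costs wording, a recalculation and a field for prior oxygen days, which the present definition already needs although Table 2 schedules oxygen therapy only from baseline. The stated power may become less favourable.

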		− 2 weeks	Baseline	24 hours	3 days	7 days	1 month	3 months	6 months	12 months	24 months
Therapy	hUC-MSCs	√	√								
	Traditional treatment	√	√	√	√	√					
Informed consent		√									
Inclusion and exclusion criteria		√	√								
Demographic information		√									
Personal history/past history/family history		√					√	√	√	√	√
Height/weight/head circumference		√	√			√	√	√	√	√	√
Vital signs^a^/physical examination		√	√	√	√	√			√	√	√
Hematology^b^/blood biochemistry^c^/urinalysis^e^		√	√	√							
Infectious disease-related examination^d^		√	√	√							
Blood oxygen saturation/blood gas analysis			√	√	√	√			√	√	√
Chromosome examination		√									
Brain MRI examination		√							√	√	√
EKG		√	√	√							
Echocardiogram		√									
Ventilator parameters/oxygen therapy			√	√	√	√	√	√	√	√	√
Adverse events evaluation			√	√	√	√	√	√	√	√	√
Chest high resolution CT			√						√	√	√
Pulmonary function test			√						√	√	√
Mortality/complications of prematurity^f^							√	√	√	√	√

Legend: *CK-MB* creatine kinase-MB*, CT*, computed tomography *EKG* electrocardiogram, *hUS-MSCs* human umbilical-cord mesenchymal stem cells

^a^The indicators of vital signs include temperature, blood pressure, heart rate, respiratory rate, transcutaneous oxygen saturation

^b^The condition of hematology of participants will be estimated by hematological tests which contains white blood cell count, platelet count, red blood cell count, hemoglobin, the percentage of lymphocytes, the percentage of neutrophil and C-reactive protein (CRP)

^c^The items of blood biochemistry include liver function, renal function, cardiac markers, the indicators of immunity, and the detailed items of each test are listed as follow. Liver function tests: albumin, bilirubin, alkaline phosphatase, alanine aminotransferase, aspartate aminotransferase, prothrombin time, activated partial thromboplastin time. Renal function tests: creatinine, blood urea nitrogen, creatinine clearance, glomerular filtration rate. Cardiac markers: hypersensitive troponin I, CK-MB mass, myoglobin

^d^Infectious disease-related examination include markers of hepatitis/syphilis/HIV/tuberculosis

^e^The content of urinalysis includes pH, protein, specific gravity, glucose and ketone bodies, white blood cells, occult blood or red blood cells, nitrite, color, and turbidity

^f^Complications of prematurity include growth retardation or retardation, hearing abnormalities, retinopathy, pulmonary hypertension, left ventricular hypertrophy

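### Table 3 limits the serious-adverse-event outcome to 24 h after infusion, which conflicts with the trial's long-term safety objective and 24-month adverse-event collection and gives the arms no stated common origin

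*Protocol article*

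**What the plan says.** The Outcome evaluation section of the protocol article refers to Table 3 for the outcome measures and their time frames. Table 3 has three adverse-event rows:

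- **Number of SAEs:** "Within 24 h post hUC-MSCs infusion".
- **Acute infusion-associated events:** "From the start of the trials to 1 month post hUC-MSCs infusion".
- **Late infusion-associated events:** up to two years after infusion.

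The text below the table gives the content of each class. For the first, "SAEs include death, any malignant cardiac event", followed by "acute pulmonary embolism, stroke, anaphylactic shock, acute transplant rejection, and any other diseases extending the hospital stay". For the second, "AIA-AEs include fever, general allergic reaction (rash, edema, erythema, pallor), infection at the injection site, vital sign changes, laboratory test changes". For the third, "LIA-AEs include tumorigenic events (tumor formation) and teratogenic events".

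The Adverse events section defines adverse events as "adverse medical events that occur after the subjects or their guardians provide written informed consent until the end of the study visit". Table 2 (under Recruitment) schedules adverse-event evaluation from Baseline to 24 months. Long-term safety is part of the first objective listed under Study objectives. The Randomization and blinding section states that controls get no cell treatment.

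**The concern.** The SAE count is the main serious-harm outcome for an intravenous cell product given to infants, and its window closes after one day. Many of the events it is meant to count could occur later, and a prolonged hospital stay can rarely be judged within 24 h. If the final report follows Table 3 literally, non-fatal serious events from day 2 onward would not be in the SAE outcome.

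The second issue is the time origin. In children this ill, background events will be frequent, and only a comparison with the control arm can separate them from harm due to the product. A window that opens at infusion has no stated start for a child who is not infused.

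**Working it through.** The plan gives no figure on this point to reproduce, and the sample size does not depend on it. The check compares the windows with the definitions and the schedule.

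**1. Share of follow-up covered.** Follow-up is 24 months, taken as 2 × 365 = 730 days. The SAE window is 1 day, so 1/730 = 0.14%. Against a 30-day first month it is 1/30 = 3.3%. These are shares of calendar time, not of events.

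**2. Share of scheduled adverse-event evaluations covered.** Table 2 ticks this row nine times: Baseline, 24 hours, 3 days, 7 days, and 1, 3, 6, 12 and 24 months. Seven of the nine (3 days onward) lie after the SAE window has closed.

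**3. Where an event after 24 h goes in Table 3.**

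| Event after 24 h | SAE row (24 h) | Acute class (to 1 month) | Late class (to 2 years) | Other Table 3 outcome |
|---|---|---|---|---|
| Death | outside | not listed | not listed | Mortality |
| Non-fatal pulmonary embolism, stroke or cardiac arrest | outside | not listed | not listed | none that names it |
| Illness prolonging hospital stay | outside | not listed as such | not listed as such | none that names it |

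Readmission counts do not fill the gap. They do not identify the event, and they miss anything that happens during the initial stay.

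**4. Time origin for controls.** The SAE window begins and ends relative to infusion. The late window is also counted from infusion. The acute window opens at the start of the trial, but its end is tied to infusion. The Follow-up procedures section likewise times visits from the injection. On the other hand, the Baseline column of Table 2 is not restricted by arm and is where the infusion is ticked, and the Statistical analysis section compares groups at baseline, 1 day, 3 days and so on. A usable day 0 therefore exists, but the SAE outcome does not refer to it.

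**5. Laboratory changes.** The acute class includes laboratory changes up to one month. In Table 2 the row "Hematology^b^/blood biochemistry^c^/urinalysis^e" has ticks at screening, baseline and 24 hours only, so the last scheduled test precedes most of that month.

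**The case against.** The strongest reply is that the data are safe. All adverse events go on the case report form, SAEs are reported in writing, and the monitoring board analyses all adverse events every six months. Deaths have their own outcome to 24 months with Kaplan-Meier analysis. The prose under Outcome evaluation also says that safety rests on counting adverse events, serious ones among them, and sets no time limit. The acute and late lists are introduced with a verb that need not make them exhaustive.

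Most of this stands, and it limits the point. A reader might infer that later serious events go unrecorded or unseen; the documents say otherwise. A reader might also infer that controls have no safety window at all. That goes too far, because the acute window opens at the start of the trial and Table 2 schedules adverse-event evaluation to 24 months without restriction by arm.

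A third tempting step is to apply the 41% mortality quoted in the Background: 24 × 0.41 = 9.8, or about 10 deaths per arm outside the SAE count. The article gives no time horizon for that 41%, the trial excludes several high-risk conditions, and deaths are counted under Mortality anyway, so the figure is not a supported expectation.

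The reply does not remove the conflict in Table 3. Recording and oversight are not the same as the defined outcome, and the unlimited prose shows that the section disagrees with its own table. Even if the two lists are not exhaustive, the article places embolism, stroke and cardiac arrest in the SAE class, and that class closes at 24 h.

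**Conclusion.** The point holds as an internal conflict in how the SAE outcome is fixed. The 24 h window covers about 0.14% of follow-up and two of nine scheduled adverse-event evaluations. It disagrees with the long-term safety objective, the adverse-event period, the Table 2 schedule and the SAE definition. What is left out in practice is non-fatal SAEs after 24 h; later deaths are captured, but only under Mortality. The comparison between arms also lacks a stated common origin, although one could be taken from Table 2.

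The conclusion rests on reading Table 3 as the definition of the outcome, which is how the section presents it. The number of events affected cannot be estimated, because the article gives no rate of non-fatal SAEs. The article does not support the inference that data are lost or that a false report of no SAEs is likely.

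**What to change.** In Table 3, define the SAE outcome as all SAEs from randomisation (or the Table 2 baseline day, whichever is chosen and stated) to 24 months in all three arms, compared between arms. Keep the count in the first 24 h after infusion as a supplementary summary for infused children.

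Reconcile the laboratory schedule in Table 2, whose last tick is at 24 h, with the one-month window of the acute class. This should not be done by restricting laboratory events to 24 h: the Adverse events section treats abnormal laboratory results as adverse events whenever they occur in the study period, and such a limit would narrow safety capture.

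For the SAE outcome, the cost is table wording and one further tabulation. The events are already collected under the Adverse events section and the Table 2 schedule.

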### Follow-up procedures

Follow-up assessments will be performed at 1, 3, 6, 12, and 24 months after the hUC-MSC injection (Table 2). The five follow-up points will be conducted by telephone and outpatient contact. The first two follow-ups will be performed at 1 and 3 months after the hUC-MSC treatment by telephone to ask the parents of the condition of their child(ren). The details of the telephone interview are shown in Table 4. The next three follow-ups will be performed at 6, 12, and 24 months at outpatient visits as shown in Table 5. The key outcome during follow-up will be changes on chest radiographs.

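### Acute infusion-associated adverse events count laboratory and infection-marker changes to 1 month, but Table 2 schedules those tests after infusion only at 24 hours, and the window opens before infusion

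*Protocol article*

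**What the plan says.** The protocol article (Outcome evaluation) lists three groups of adverse events as secondary safety outcomes: serious, acute infusion-associated and late infusion-associated. Table 3 gives the acute group the time frame "From the start of the trials to 1 month post hUC-MSCs infusion".

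The text below Table 3 gives the acute group two kinds of content:

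- Clinical: "AIA-AEs include fever, general allergic reaction (rash, edema, erythema, pallor), infection at the injection site, vital sign changes".
- Laboratory: "laboratory test changes (indicators of liver and kidney function, cardiac markers, indicators of hematology and immunity, markers of hepatitis/syphilis/HIV/tuberculosis, and urinalysis".

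Table 2 (under Recruitment) sets the visit schedule. The rows "Hematology^b^/blood biochemistry^c^/urinalysis^e" and "Infectious disease-related examination^d" are each ticked at 2 weeks before, baseline and 24 hours, and nowhere later. The row "Adverse events evaluation" is ticked from baseline through every later time point.

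Follow-up procedures adds: "The first two follow-ups will be performed at 1 and 3 months after the hUC-MSC treatment by telephone".

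**The concern.** The outcome definition and the visit schedule disagree. The definition promises laboratory and infection-marker changes to 1 month, while the schedule stops looking for them at 24 hours. A change that produces no symptoms and first appears on day 2 or later would come to light only if someone happened to order the test.

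No other outcome in Table 3 fills the gap. The count of serious events runs to 24 hours, and the late group names only tumor and teratogenic events. The acute group is therefore the only listed adverse-event outcome that covers non-serious toxicity between day 2 and 1 month.

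The start of the window is also loose. An outcome called infusion-associated begins at the start of the trial, so something that happened before any cells were given can be counted in it.

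Safety is a stated goal of the trial, and two doses are compared with control. What is at stake is whether the trial can say anything about laboratory toxicity or infection markers up to the 1 month that Table 3 names.

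**Working it through.** The plan states no figure on this point that could be reproduced. The check sets the schedule against the definition.

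**Step 1. Scheduled post-infusion coverage within the 1-month window (from Table 2).**

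| Component | 24 h | 3 d | 7 d | 1 month |
|---|---|---|---|---|
| Hematology, biochemistry, urinalysis | yes | no | no | no |
| Infection markers | yes | no | no | no |
| Vital signs, physical examination | yes | yes | yes | no |
| Adverse-event evaluation | yes | yes | yes | yes |

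The laboratory and infection-marker components are tested at 1 of 4 time points, vital signs at 3 of 4, and adverse events are evaluated at 4 of 4. Blood gas analysis continues at 3 and 7 days, but it is not in the laboratory list that defines this outcome.

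**Step 2. Can the 1-month contact supply the tests?** No. It is made by telephone, and Table 2 ticks none of these tests there. The telephone list (Table 4) is not visible in the text at hand, but a telephone call cannot itself provide a sample.

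**Step 3. Sensitivity to table extraction.** Suppose the ticks had slipped one column, so that they belong at baseline, 24 hours and 3 days. The tests would then fall at 2 of 4 time points, with nothing at 7 days or 1 month. With a 30-day month, 30 − 3 = 27 days would still follow the last scheduled test. The mismatch does not depend on exact column alignment.

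**Step 4. What a zero count would mean.** With 24 infants per arm and no laboratory event seen, the one-sided 95% upper bound on the event rate is 1 − 0.05^(1/24) = 0.117, or 11.7%. For laboratory changes, scheduled testing would support that bound only for what is visible by 24 hours. The label in Table 3 would invite reading it as a 1-month bound.

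**Step 5. The start of the window.** Three starting points appear:

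- Table 3: the start of the trial.
- Adverse events section: written consent.
- Table 2: adverse-event evaluation from baseline, with screening 2 weeks earlier.

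None of these is the infusion. The control arm has no infusion, so the article's wording gives controls no matching day 0 for this outcome.

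**The case against.** The strongest reply is that the outcome is wider than its laboratory part and that most of it is observed. Fever, allergic reaction and injection-site infection are picked up by adverse-event evaluation at 3 days, 7 days and 1 month, and vital signs are checked at 3 and 7 days. The Adverse events section counts abnormal laboratory results as adverse events and requires all of them on the case report form, so a clinically prompted abnormal test would be recorded. This stands, and it limits the point to changes that scheduled testing alone would find. It does not close the gap. After 24 hours a laboratory result exists only if someone orders the test, and in an open-label trial ordering may differ between arms.

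A reader might infer more than the documents support:

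- **That the whole outcome goes unmeasured after 24 hours.** Step 1 shows that this is true only of the laboratory and infection-marker parts.
- **That a clean 24-hour result will be reported as no toxicity to 1 month.** No section says so.
- **That an infection passed on by the product could not be detected.** Diagnosed disease is itself an adverse event under the article's definition. Nor can one be sure that markers are never retested: Table 2 shows no later tick, but the outpatient list (Table 5) is not visible.
- **That this is the trial's main dose-toxicity outcome.** The article does not rank the safety outcomes, and its sample-size section says that the trial is not powered to compare the two doses.
- **That the share of untested days measures the problem.** After a 24-hour test, 29 of 30 days (97%) remain, but testing at separate time points always leaves most days untested. Adding a day-7 panel would still leave 28 of 30 (93%). The count of scheduled time points is the fairer measure.
- **That 14 of 44 days (32%) of the window precede infusion.** This assumes that screening lasts the full 14 days and that the window opens on its first day, while Table 2 starts adverse-event evaluation at baseline. Randomization follows baseline data collection, so events before randomization are balanced in expectation. They add noise rather than bias.

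**Conclusion.** The point holds in a limited form. The definition under Outcome evaluation and Table 3 does not match the schedule in Table 2. For laboratory and infection-marker changes, 1 of the 4 post-infusion time points in the window has a scheduled test. Changes arising later can be missed in any arm, unscheduled testing may differ by arm, and the 1-month rate cannot be estimated as defined. Separately, the window admits events from before infusion.

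Severity is moderate. One component of a secondary safety outcome is affected. The primary outcome, sample size and randomization are not touched.

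The conclusion assumes that Tables 2 and 3 are read as they appear in the text, with the sensitivity in Step 3, and that no later scheduled test sits in the lists that are not visible.

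**What to change.** Reconcile Table 2 with Table 3. Either of two routes is enough, and the choice is the sponsor's:

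1. **Match the outcome to the schedule.** Restate the laboratory and infection-marker part of the outcome as covering the first 24 hours after infusion, and draw no conclusion on laboratory toxicity to 1 month. The clinical part keeps its 1-month frame. The cost is a text amendment with no added sampling.
2. **Match the schedule to the outcome.** Schedule the listed tests, in all three arms alike, at a later contact already in Table 2, and give them a time frame in Table 3 that ends where the last test is taken. Infection markers may need a frame of their own. The cost is some additional sample volume and possibly more laboratory events reported. The article gives no sample volumes, so the burden cannot be sized from it.

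Under either route, open the acute window at infusion, define a matching day 0 for controls, and list earlier events separately as pre-treatment. This is a wording change only.
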